## Abstract

**Background:**

Overt chronic metabolic acidosis in patients with chronic kidney disease develops after a drop of glomerular filtration rate to less than approximately 25 mL/min/1.73 m^2^. The pathogenic mechanism seems to be a lack of tubular bicarbonate production, which in healthy individuals neutralizes the acid net production. As shown in several animal and human studies the acidotic milieu alters bone and vitamin D metabolism, induces muscle wasting, and impairs albumin synthesis, aside from a direct alteration of renal tissue by increasing angiotensin II, aldosteron and endothelin kidney levels. Subsequent studies testing various therapeutic approaches in very selected study populations showed that oral supplementation of the lacking bicarbonate halts progression of decline of renal function. However, due to methodological limitations of these studies further investigations are of urgent need to ensure the validity of this therapeutic concept.

**Methods/Design:**

The SoBic-study is a single-center, randomized, controlled, open-label clinical phase IV study performed at the nephrological outpatient service of the Medical University of Vienna. Two-hundred patients classified to CKD stage 3 or 4 with two separate measurements of HCO_3_^-^ of <21 mmol/L will be 1:1 randomized to either receive a high dose of oral sodium bicarbonate with a serum target HCO_3_^-^ level of 24 ± 1 mmol/L or receive a rescue therapy of sodium bicarbonate with a serum target level of 20 ± 1 mmol/L. The follow up will be for two years. The primary outcome is the effect of sodium bicarbonate supplementation on renal function measured by means of estimated glomerular filtration rates (4-variable-MDRD-equation) after two years. Secondary outcomes are change in markers of bone metabolism between groups, death rates between groups, and the number of subjects proceeding to renal replacement therapy across groups. Adverse events, such as worsening of arterial hypertension due to the additional sodium consumption, will be accurately monitored.

**Discussion:**

We hypothesize that sufficiently balanced acid–base homeostasis leads to a reduction of decline of renal function in patients with chronic kidney disease. The concept of an exogenous bicarbonate supplementation to substitute the lacking endogenous bicarbonate has existed for a long time, but has never been investigated sufficiently to state clear treatment guidelines.

**Trial registration:**

EUDRACT Number: 2012-001824-36

## Background

Chronic kidney disease (CKD) occurs in approximately one in ten persons worldwide and represents not only a medical challenge but also a great socioeconomic burden. Major efforts have been made to investigate treatment options aiming to slow progression to end-stage renal disease (ESRD) and, subsequently, to reduce mortality in kidney patients. A renin-angiotensin system blockade with either angiotensin-I-converting enzyme inhibitors or angiotensin-II-receptor antagonists slows the progression of decline in renal function [1-5]. However, further therapeutic interventions have not shown any benefits [6-10]. The comprehensive summery by Fink *et al.* underscores the lack of evidence-based treatment concepts in CKD and even calls screening and monitoring for early-stage CKD into question [11].

Overt chronic metabolic acidosis in CKD patients develops after a drop in glomerular filtration rate (GFR) to less than approximately 25 mL/min/1.73 m^2^. The pathogenic mechanism seems to be a lack of tubular bicarbonate production, which in healthy individuals neutralizes the acid net production. As shown in several animal and human studies the acidotic milieu alters bone and vitamin D metabolism [12], induces muscle wasting [13], and impairs albumin synthesis [14], in addition to other detrimental effects [15,16]. Experiments in rats suggest that even in the earlier stages of CKD with serum bicarbonate levels within normal limits, increased per-nephron acidification occurs to obviate overt metabolic acidosis [17]. Investigations to elucidate the contribution to the progression of CKD itself have provided contradictory results [18-20]. However, there is evidence that the alternative complement system is activated by increased tubular ammonia production [21] and that endothelin, angiotensin II and aldosteron kidney concentrations are increased as a direct result of distal nephron acidification [17,20,22]. Taken together, these alterations induce tubulointerstitial scarring in the long term.

The results of several retrospective studies conducted in different types of populations showed clear associations between acid–base imbalance and increased mortality [23,24]. Above all is the recently published analysis of the CKD registry of the Cleveland Clinic health care provider in 41,749 patients with CKD stage III and IV (estimated (e) GFR of 60 to 15 mL/min/1.73 m^2^, measured by the Chronic Kidney Disease Epidemiology Collaboration equation). Adjusted for several covariates the all-cause mortality for subjects with a low serum bicarbonate level (<23 mmol/L) is 23% higher than for those with a level within the normal range (23 to 32 mmol/L) [25].

The first prospective studies in closely selected study populations [26] using various therapeutic interventions [27] and endpoints revealed beneficial effects. In particular, de Brito-Ashurst *et al.* showed that sodium bicarbonate supplementation in patients with CKD stage IV slows the decline in renal function, although the study comprised some serious methodological limitations [28].

In line with the aforementioned studies we assume that a sufficiently balanced acid–base status leads to a reduction in the decline of renal function in patients with CKD. Bicarbonate is necessary to counterbalance acid net production arising from protein metabolism and acid-rich diets. Thus, the intervention of exogenous bicarbonate supplementation to substitute the lacking endogenous bicarbonate would appear to be rational. This simple concept has existed for a long time, but has never been investigated sufficiently to state clear treatment guidelines for physicians. Furthermore, including patients with both moderate and severe grades of renal impairment represents a novel and comprehensive approach. Thus, conclusions drawn by results of this study are directly applicable to routine care and treatment guidelines.

## Methods/Design

### Trial design

The SoBic study is a single-center, randomized, controlled, stratified, open-label clinical phase IV study and will be performed at the Nephrological outpatient service of the Medical University of Vienna. From the beginning of October 2013, 200 subjects with CKD stage III and IV and chronic metabolic acidosis will be randomized to either receive a high dose of oral sodium bicarbonate with a serum target HCO_3_^-^ level of 24 ± 1 mmol/L or receive a rescue therapy of sodium bicarbonate, if necessary, with a serum target level of 20 ± 1 mmol/L. The follow up period will be 2 years. The ethics committee of the Medical University of Vienna and the Austrian Competent Authority approved the study. The study is registered at the European Union Drug Regulating Authority (EUDRACT Number: 2012-001824-36; https://www.clinicaltrialsregister.eu) and will be conducted in accordance with the current version of the Declaration of Helsinki [29]. All study subjects will be appropriately insured and are required to give written informed consent before any study action is taken. Data will be stored in the Clincase version 2.6.0.33 clinical trial system (Quadratek Data Solutions Ltd, London, United Kingdom. Data structure design is developed by the science support work group of AKIM (Allgemeines Krankenhaus Informations Management) at the Center of Medical Statistics, Informatics and Intelligent Systems. The software provides advanced data management and data preparation tools for statistic evaluation. The web-based electronic case report forms allow efficient user handling and thus, error avoidance. In accordance with the Good Clinical Practice (GCP) guidelines an independent person will periodically perform data monitoring [30]. The study will be reported as suggested by the Consolidated Standards of Reporting Trials (CONSORT) 2010 guidelines [31].

### Participants

The study population will comprise incident and prevalent patients with CKD from the outpatient service of a tertiary care facility. Patients classified as having CKD stage III or IV, and two separate measurements of HCO_3_^-^ of <21 mmol/L (at least 1 day apart) will be included in the study. Patients fulfilling the inclusion criteria, who are already receiving alkali treatment, can be included after a wash-out phase of 4 weeks. The inclusion criteria are age over 18 years, renal function (measured by eGFR calculated by the four-variable Modification of Diet in Renal Disease (MDRD) study equation) between 60 and 15 mL/min/1.73 m^2^, venous serum HCO_3_^-^ of <21 mmol/L on two consecutive measurements (at least 1 day apart), and for the patient to be in a stable clinical condition. Patients with malignant disease or within 5 years of successful treatment of malignant disease (except dermal malignancies and carcinoma *in situ* of the cervix declared to be cured), and patients with morbid obesity (body mass index >40 kg/m^2^), chronic inflammation (C reactive protein >10 mg/dL) or taking immunosuppressive therapy of any kind, poorly controlled blood pressure (>150/90 mmHg despite the use of four agents), overt congestive heart failure, or known peanut or soy allergy, will be excluded from the study.

With respect to concomitant medication, various drugs are known to induce metabolic acidosis [32]. However, most relevant with regard to the planned study are the phosphate binder sevelamer hydrochloride and potassium-sparing diuretics. Other agents known to neutralize metabolic acidosis, such as calcium citrate, sodium citrate and calcium carbonate are not allowed.

### Laboratory measurements

Serum creatinine will be determined by means of the Jaffe method (reference range <1.2 mg/dL, mg/dL × 88.4 = μmol/L). Bicarbonate measurements will be performed in venous blood samples and determined by an ABL 700 Copenhagen Blood Gas Analyzer (Radiometer Copenhagen, Copenhagen, Denmark). Markers of bone metabolism (bone alkaline phosphatase, osteocalcin, c-telopeptide pyridinoline crosslinks of type I collagen, procollagen type I N-propeptide) will be measured as detailed in Cejka *et al.*[33]. All laboratory measurements, including urinalyses, will be performed in an ISO 9001–2008 certified and ISO 15189-accredited clinical laboratory at the Medical University Vienna [http://www.kimcl.at].

### Randomization and study visits

Subjects will attend the clinic for a regular visit and blood draw. After a careful review of their medical history patients who fulfill the inclusion criteria will be contacted and informed about the study protocol. Patients who agree to participate in the study will be invited to a further blood work-up to ensure that metabolic acidosis is chronic rather than a one-time imbalance of the acid–base status. After obtaining written informed consent (day 0) each patient will be randomized 1:1 either to the treatment group or the control group (Figure 1). Subjects will be stratified for age >60 years and ≤60 years [34], presence of diabetes mellitus (yes/no) [35], severe chronic metabolic acidosis (serum HCO_3_^-^ <18 mmol/L) versus moderate metabolic acidosis (serum HCO_3_^-^ ≥18 mmol/L), and for previous alkali treatment (yes/no). Previous alkali treatment is defined as being continued for longer than 6 months (>25% of the treatment period of the planned study) and serum HCO_3_^-^ ≥20 mmol/L on more than 75% of measurements. Stratified randomization will be carried out using the web-based randomizer program provided by the Medical University of Vienna [https://www.meduniwien.ac.at/randomizer/web/login.php]. We use the minimization method with a preferred treatment probability of 0.9, and a combination depth of 2.0, to guarantee that treatment allocation is balanced in all levels of the stratification factors, as well as in all pairwise combinations of stratification factors. After randomization, subjects will receive either the high dose of sodium bicarbonate or, if necessary, a low-dose rescue therapy with sodium bicarbonate.

**Figure 1 F1:**
[figure not shown]
**Study design. **^*^Two consecutive measurements at least 1 day apart. CKD, chronic kidney disease.

Each study visit consists of a fasting blood draw (last food intake including the study medication should be at least 8 hours before) and urinalysis, measurement of vital signs, and assessment of changes in concomitant medication and adverse events (Table 1). At the beginning of the study a physical examination will be done and body weight and height will be assessed. Study visits will be performed at weeks 4, 8, 12, 20, 29, 38, 47, 60, 73, 86, and 104.

**Table 1 T1:** Visit and assessment schedule

	**Screening period (4 weeks)**							**Treatment period (0 to 24 months)**					
		**Day 0**	**Week 4**	**Week 8**	**Week 12**	**Week 20**	**Week 29**	**Week 38**	**Week 47**	**Week 60**	**Week 73**	**Week 86**	**Week 104**
			**(± 2 days)**	**(± 2 days)**	**(± 2 days)**	**(± 5 days)**	**(± 5 days)**	**(± 5 days)**	**(± 5 days)**	**(± 10 days)**	**(± 10 days)**	**(± 10 days)**	**(± 10 days)**
**Visit**	1	2	3	4	5	6	7	8	9	10	11	12	13
**Informed consent**		x											
**Inclusion/exclusion criteria**	x	x											
**Randomization**		x											
**Medical history**		x											x
**Concomitant medication**		x	x	x	x	x	x	x	x	x	x	x	x
**Physical examination**		x											x
**Body weight and height**		x											x
**Vital signs (BP, PR)**		x	x	x	x	x	x	x	x	x	x	x	x
**Laboratory test**	x	x	x	x	x	x	x	x	x	x	x	x	x
**Laboratory test: bone markers**		x				x							x
**Biobank sample**		x				x			x		x		x
**Urinalysis**	x	x	x	x	x	x	x	x	x	x	x	x	x
**24-hour urine collection**	x^a^	x^a^	x			x			x				x
**Urine pregnancy test**^**b**^		x	x	x	x	x	x	x	x	x	x	x	x
**Adverse events**			x	x	x	x	x	x	x	x	x	x	

^**a**^To be performed either at screening visit 1 or screening visit 2. prior to randomization; ^**b**^for females of childbearing age only. BP, blood pressure; PR, pulse rate.

### Intervention

The initial and the maintenance dose for the intervention group will be determined based on the baseline HCO_3_^-^ level and the levels measured during follow up visits. Based on pilot data we expect the daily dose for the intervention group to vary between two and six capsules of Nephrotrans® 840 mg (1,680 to 5,040 mg sodium bicarbonate per day). In the case of HCO_3_^-^ lower than 19 mmol/L at the baseline visit, or during follow up, subjects randomized to the control group will receive rescue therapy. We expect the daily dose to be zero to three capsules of Nephrotrans® 840 mg (0 to 2,520 mg sodium bicarbonate per day) for the control group. After each study visit the study drug can be down- and up-titrated according to the actual HCO_3_^-^ level and the respective target value, as pre-specified at randomization, by means of the suggested treatment algorithm (Table 2A and B). However, due to intra-individual differences in drug response the algorithm is not obligatory and might be modified if necessary to reach the target HCO_3_^-^ level for respective subjects.

**Table 2 T2:** Study drug up- and down-titration

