	**Daily sodium bicarbonate (Nephrotrans® 840 mg) dosage**	
**(A) Baseline treatment algorithm**	Investigational group	Control group
Mean HCO_3_^-^ of two measurements		
<18 mmol/L	5,040 mg (2 capsules TID)	2,520 mg (1 capsule TID)
18 to 19 mmol/L	4,200 mg (2 capsules BID, 1 capsule QD)	1,680 mg (1 capsule BID)
19.1 to 20.0 mmol/L	2,520 mg (1 capsule TID)	Monitor
>20 mmol/L	1,680 mg (1 capsule BID)	
**(B) Follow-up visit treatment algorithm**	Investigational group and control group	
Difference to target HCO_3_^-^ level		
−1 mmol/L	Add 1,680 mg to the previous daily dosage (+1 capsule BID)	
−2 mmol/L	Add 3,360 mg to the previous daily dosage (+2 capsules BID)	
≤ −3 mmol/L	Add 5,040 mg to the previous daily dosage (+2 capsules TID)	
+1 mmol/L	Subduct 1,680 mg from the previous daily dosage (−2 capsules)	
+2 mmol/L	Subduct 3,360 mg from the previous daily dosage (−4 capsules)	
≥ +3 mmol/L	Subduct 5,040 mg from the previous daily dosage (−6 capsules)	

QD, every day; BID, twice daily; TID, trice daily.

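### The protocol gives no single consistent default dosing rule: text and Table 2A differ at 19.0 mmol/L and on which baseline value counts, and Table 2B's steps do not fit the expected dose ranges

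*Protocol article*

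**What the plan says.** The Trial design section sets a bicarbonate "level of 24 ± 1 mmol/L or receive a rescue therapy of sodium bicarbonate, if necessary", the latter "with a serum target level of 20 ± 1 mmol/L". The bands are thus 23 to 25 mmol/L (intervention) and 19 to 21 mmol/L (control).

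The Intervention section gives the control trigger: for a value "lower than 19 mmol/L at the baseline visit, or during follow up, subjects randomized to the control group will receive rescue therapy". It also forecasts doses. For the intervention arm, "we expect the daily dose for the intervention group to vary between two and six capsules" (1,680 to 5,040 mg). For the control arm, "We expect the daily dose to be zero to three capsules" (0 to 2,520 mg). The section on randomization and study visits describes control treatment as rescue at a low dose, given only if needed.

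Table 2A sets the starting dose from the mean of two measurements. Its control entry for 18 to 19 mmol/L is "1,680 mg (1 capsule BID"). The next row starts at 19.1 mmol/L and says only to monitor.

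Table 2B adjusts the dose at follow-up by the difference from target, with the same steps in both arms. At 1 mmol/L below target: "Add 1,680 mg to the previous daily dosage (+1 capsule BID"). At 3 mmol/L or more below: "Add 5,040 mg to the previous daily dosage (+2 capsules TID"). The decreases above target mirror the increases.

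The Intervention section calls the algorithm a suggestion that may be modified to reach the target.

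**The concern.** The trial compares two bicarbonate targets in an open-label design, so the dosing rule is the intervention. A clinician who follows the text and one who follows the tables should arrive at the same default action for the same patient. In places they do not.

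Two things could be at stake. The first is sodium load, which the Discussion itself names as a concern. Followed mechanically, Table 2B leads to doses well above those the article forecasts. The second is the clarity of the comparison, since a control patient can be moved to a dose above the forecast intervention range.

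**Working it through.** **Inputs.** One capsule is 840 mg (Intervention). Bands, trigger and expected ranges are as given above. Table 2A control doses: 2,520 mg below 18 mmol/L, 1,680 mg for 18 to 19, monitoring for 19.1 to 20.0 (read here as 0 mg). Table 2B steps: +1,680 mg at −1, +3,360 mg at −2, +5,040 mg at −3 or lower. Sodium: 27.4 mg per 100 mg of drug (Discussion).

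**The plan's own figures.** 2 × 840 = 1,680; 3 × 840 = 2,520; 6 × 840 = 5,040. Table 2A runs from 0 to 2,520 mg in control and from 1,680 to 5,040 mg in intervention, which reproduces both expected ranges exactly. The trigger below 19 also agrees with the lower edge of the control band. The problems lie elsewhere.

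**1. Control value of exactly 19.0.**
- Text: not below 19, so no rescue.
- Target band: 19 is inside 19 to 21.
- Table 2A: 19.0 falls in the 18-to-19 row, because the next row starts at 19.1, so 1,680 mg.

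**2. Which baseline value.** Hypothetical patient: 19.6 at screening and 18.8 at the baseline visit. By the text, 18.8 is below 19 and rescue is given. By Table 2A, (19.6 + 18.8) / 2 = 19.2 and the patient is monitored.

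**3. Reference point of Table 2B.** Centre reading: difference = value − 20 (control) or value − 24 (intervention). Edge reading: difference from the nearer limit of the band, and zero inside it.
- Centre: 19 and 21 (control) and 23 and 25 (intervention) are each 1 mmol/L off, so each triggers a 1,680 mg change although all are within target.
- Edge: none of these values triggers a change.

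**4. Table 2B against the expected ranges.** New dose = previous dose + step.

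| Patient | Edge reading | Centre reading | Expected maximum |
|---|---|---|---|
| Control on 1,680 mg, smallest increase | 1,680 + 1,680 = 3,360 | same | 2,520 |
| Control on 2,520 mg, smallest increase | 2,520 + 1,680 = 4,200 | same | 2,520 |
| Control untreated, at 17 | 0 + 3,360 = 3,360 | 0 + 5,040 = 5,040 | 2,520 |
| Control on 2,520 mg, at 17 | 2,520 + 3,360 = 5,880 | 2,520 + 5,040 = 7,560 | 2,520 |
| Intervention on 1,680 mg, at 20 | 1,680 + 5,040 = 6,720 | same | 5,040 |
| Intervention on 5,040 mg, at 21 | 5,040 + 3,360 = 8,400 | 5,040 + 5,040 = 10,080 | 5,040 |

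The fourth row exceeds the intervention arm's expected maximum of 5,040 mg on both readings.

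**Sodium for the last row.** 8,400 × 0.274 = 2,302 mg per day; 10,080 × 0.274 = 2,762 mg per day. At the expected maximum it would be 5,040 × 0.274 = 1,381 mg per day.

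**The case against.** The strongest reply is that Table 2 is only a guide. The fixed element is the target, the algorithm may be modified, and the dose ranges are worded as expectations. This stands: no patient must receive 7,560 or 10,080 mg, and a dose outside a range breaks no rule. It does not reconcile the printed rules, because permission to deviate still presupposes one default to deviate from.

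Second, the changes inside the band depend on the centre reading, which the document does not state. This also stands, so item 3 is an ambiguity and not an error. Items 1, 2 and 4 do not depend on it.

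Third, Table 2A sets a starting dose and Table 2B adjusts an existing one, so different doses at 17 mmol/L need not be a contradiction: a patient still at 17 on 2,520 mg has responded poorly. That is fair for treated patients. It does not explain why the steps leave the forecast range, and for an untreated control patient who falls to 17 there is no previous response to account for.

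Fourth, the single-versus-mean difference may be loose wording in a condensed article. That is possible, but the two statements can lead to opposite actions.

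A reader might go further and infer that trigger, band, tables and ranges all contradict one another, or that the separation between arms shrinks. The documents support neither. The trigger agrees with the band, and Table 2A agrees with the ranges. Dosing still aims at targets 4 mmol/L apart, values above target lower the dose, and no figure in the protocol gives the size of any loss of separation.

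**Conclusion.** The point holds as a set of inconsistencies in the default dosing guide. A control value of 19.0 mmol/L gets 0 or 1,680 mg depending on the place consulted, the baseline value to use is stated in two ways, and Table 2B lacks a reference point. Whatever that reference point is, Table 2B does not fit the forecast ranges or the description of control treatment as low-dose. The smallest increase from a Table 2A control dose already exceeds the control forecast (3,360 or 4,200 against 2,520 mg), and the examples reach 5,880 to 7,560 mg in control and 8,400 to 10,080 mg in intervention.

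These doses assume that the table is applied as printed, without the modification the protocol allows. Higher sodium exposure is a possible consequence. A blurred contrast between arms is conceivable but not shown. The sample size calculation is not affected by this point.

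**What to change.** Before first dosing, the clinical team should reconcile the Trial design, Randomization and study visits, and Intervention sections with Tables 2A and 2B, and state:

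- one rule for a control value of exactly 19.0 mmol/L;
- whether the baseline-visit value or the mean of two measurements applies at baseline;
- whether Table 2B differences are counted from the centre or the edge of the band, and what happens to values inside the band;
- how the Table 2B steps relate to the expected dose ranges and to the low-dose description of control treatment.

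Which dose or threshold is right is for that team to decide, and none is proposed here. The cost is a change of wording. Bicarbonate is already measured at every visit, so no extra visits or data are needed.
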